### 9.2 Falls and fall-related injuries

The proportion of falls and injuries due to falls at each time point and their 95% confidence intervals will be calculated for each group.

### 9.3 Unscheduled hospital visit

If a participant visited hospital without appointment, it will be treated as unscheduled visit regardless of the reason for the visit. The rate of unscheduled visit and its 95% confidence interval at each time point will be calculated for each group.

#### 9.4 Health-related quality of life score (EQ-5D Japanese version)

Descriptive statistics for the EQ-5D scores at admission and at 6 and 12 months will be calculated according to group allocation.

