## **15. Sample size calculation and its rationale**

Based on previous studies, we estimate the event rate at 12 months for the primary endpoint to be 30% for the intervention group and 40% for the control group. Assuming equally spaced enrollment and allocation, a total of 423 subjects would be needed for the analysis to have a power of 0.80 with a two-sided test at a significance level of 0.05. We estimate 15-20% exclusion from the analysis and plan to enroll a total of 500 subjects (250 in each group) over the 2-year period.

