## 4. Data handling

### 4.1 Handling of missing data and outlier

#### Handling of missing data

In case of missing data, no imputation will be performed. However, if it is known before the data are fixed that there are missing values that may have a significant impact on the analysis results, methods to deal with the missing values will be described in this analysis plan.

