## 5. Definition related to statistical analysis

### 5.1 Definition related to statistical analysis methods

- Descriptive statistics for categorical data will be count and proportion for each category.

- Descriptive statistics for continuous data will be the number of persons, mean, standard deviation, median, 25th percentile, 75th percentile, minimum and maximum.
- Two-sided test with a significance level of 0.05 will be used for group comparison.

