#### 9.6 Number of regularly prescribed medications and drug name

Descriptive statistics of the number of medications taken at admission, discharge, and 6 and 12 months after study enrollment and the proportion of drug names will be calculated for each group.

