#### 9.7 Number of potentially inappropriate medications and drug name

The number of potentially inappropriate prescriptions is defined as the number of medications that meet STOPP criteria, and the names of medications that meet STOPP criteria are defined as potentially inappropriate drug names. Descriptive statistics of the number of potentially inappropriate prescriptions and the proportion of potentially inappropriate drug names will be calculated for each group at admission, discharge, and 6 and 12 months after study enrollment.

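### EQ-5D, care level, number of medications and number of STOPP medications have no planned between-arm estimate, no baseline adjustment and no rule for deaths

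*Combined protocol and SAP*

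**What the plan says.** Protocol section 7(2) lists all four as secondary endpoints. Protocol section 14(2) leaves the methods for secondary endpoints to the SAP, so the SAP is the only place where a comparison could be defined.

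- EQ-5D (SAP 9.4): "Descriptive statistics for the EQ-5D scores at admission and at 6 and 12 months will be calculated according to group allocation".
- Care level (SAP 9.5): the level at admission, 6 and 12 months, with a 95% CI for each group.
- Number of medications (SAP 9.6): "Descriptive statistics of the number of medications taken at admission, discharge, and 6 and 12 months after study enrollment", by group.
- STOPP medications (SAP 9.7): "Descriptive statistics of the number of potentially inappropriate prescriptions and the proportion of potentially inappropriate drug names will be calculated for each group", at the same four times.

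SAP 5.1 gives a general rule, "Two-sided test with a significance level of 0.05 will be used for group comparison", but attaches no test or model to these endpoints. On missing data, SAP 4.1 says: "In case of missing data, no imputation will be performed". It adds that methods will be written into the plan if influential missing values become known before the data are fixed. No such method appears. Nothing says how a death before 6 or 12 months enters these four endpoints.

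Baseline values of all four are collected (protocol section 8 and its timetable), and randomisation is stratified by three age groups (protocol section 6(5)).

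**The concern.** A randomised trial reports an effect as a contrast between arms with its uncertainty. For these four endpoints the plan stops one step short: it produces the two columns but not the difference between them.

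The drug counts matter most. The team only proposes changes and the attending physician decides (protocol section 3), so whether prescribing changed is an open question in this trial. A null primary result means one thing if prescribing moved and another if it did not. A planned estimate of the difference in drug and STOPP counts is what separates the two.

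For EQ-5D and care level there is a further difficulty. The participants are inpatients aged 65 or over, excluded on prognosis only if life expectancy is under one month, and death is part of the primary endpoint. Some will die before 6 or 12 months. If deaths simply drop out, the later figures no longer compare the groups as randomised.

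**Working it through.** **1. Which endpoints get a contrast**

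| Endpoint | SAP | Within arm | Between arms |
|---|---|---|---|
| Rehospitalization, unscheduled visit, death | 8.2–8.4 | Kaplan-Meier | stratified log-rank, Cox hazard ratio |
| Death during initial hospitalization | 9.1 | Kaplan-Meier | log-rank |
| EQ-5D | 9.4 | descriptive | none |
| Care level | 9.5 | level with 95% CI | none |
| Number of medications | 9.6 | descriptive | none |
| STOPP medications | 9.7 | descriptive | none |

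The gap is specific to the last four rows.

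**2. The plan's own figure**

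No SD, target difference or power is given for the four endpoints. The only sample size is for the primary endpoint (protocol section 15): "a total of 423 subjects would be needed for the analysis to have a power of 0.80", from rates of "30% for the intervention group and 40% for the control group".

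- HR = ln 0.70 / ln 0.60 = 0.698.
- Events (Schoenfeld) = 4 × (1.96 + 0.8416)² / (ln 0.698)² = 244.
- Uniform 2-year accrual with a common close at year 3: P(event) = 1 − (e^−λ − e^−3λ)/(2λ). This is 0.624 for λ = 0.511 and 0.500 for λ = 0.357, mean 0.562.
- N = 244 / 0.562 = 434, within 3% of 423.

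This reproduces 423 only under a common close, which is a separate matter. Here 423 serves only as a plausible number with data; the plan's allowance ("We estimate 15-20% exclusion from the analysis") gives 400 to 425 of 500.

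**3. Precision with and without baseline**

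The 95% CI half-width of a mean difference, in SD units, is 1.96 × √(4/N) × √(1 − r²), where r is the correlation between baseline and follow-up. The documents give no r, so a range is assumed.

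| With data | Unadjusted | r = 0.3 | r = 0.5 | r = 0.7 |
|---|---|---|---|---|
| 423 | 0.191 | 0.182 | 0.165 | 0.136 |
| 300 (assumed) | 0.226 | 0.216 | 0.196 | 0.162 |

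The variance cut is r² = 9%, 25%, 49%. The interval narrows by 1 − √(1 − r²) = 5%, 13%, 29%.

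**4. Per-arm intervals do not stand in for the difference**

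For a mean, each arm's half-width is 1.96 × √(2/N) SD, or 0.135 at N = 423. Two such intervals stop overlapping only at a difference of 2 × 0.135 = 0.270 SD, against 0.191 SD for the CI of the difference to exclude zero. The ratio is √2 = 1.41. A reader comparing separate intervals, as SAP 9.5 invites for care level, applies a much stricter criterion than intended.

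**5. Deaths**

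Suppose survivors in both arms have the same mean EQ-5D, m. The survivor difference is then 0 whatever the mortality. With death scored 0, the difference is m × (control mortality − intervention mortality). All values are assumed:

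- equal mortality: 0;
- 20% vs 15%, m = 0.65: 0.65 × 0.05 = 0.0325 (0.030 to 0.035 for m = 0.60 to 0.70);
- 20% vs 10%, m = 0.65: 0.65 × 0.10 = 0.065 (0.060 to 0.070).

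This shows that the two summaries answer different questions once mortality differs. It says nothing about which way this trial would go.

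**The case against.** Much of the case on the other side is right and limits the point.

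- **Other secondary endpoints are compared between arms**, as the first table shows. Falls (SAP 9.2) also gets only per-arm proportions with CIs, but it has no follow-up score to adjust and is not part of this point.
- **The baseline is not ignored.** Admission values are tabulated by group beside the later ones. They are only left out of any comparison.
- **The information is not lost.** SAP 5.1 defines descriptive statistics to include n, mean and SD, so anyone can form a crude difference. A reader might infer that the trial cannot say whether prescribing changed. The documents do not support that; what is missing is a planned, adjusted estimate.
- **No text restricts these analyses to survivors.** A reader might take that as the stated design. It is an inference from no imputation plus silence on death. Next of kin are interviewed when the participant cannot be, and community pharmacies supply drug data, so non-response is mitigated. Neither measure deals with death.
- **Scoring death as 0 is debatable.** It mixes mortality, already analysed separately, into quality of life, and it needs an index anchored at 0 for death. The documents name no value set.
- **More contrasts add multiplicity.** Protocol section 14(2) already states that tests are unadjusted.

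Two further readings are tempting. One is that better survival in an arm will pull its mean EQ-5D down; the illustration assumes equal survivor means and does not show this. The other is that baseline EQ-5D follows allocation, because the timetable marks it in the enrollment column. Both columns are week 0, protocol section 8(3) describes a face-to-face baseline survey, SAP 9.4 says admission, and no passage places it after allocation.

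What stands after all this: no planned between-arm estimate, no use of baseline or age strata in a comparison, and no rule for deaths, for these four endpoints.

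**Conclusion.** The point holds for the four named endpoints and no further. It should be corrected, but it does not touch the primary test or its conclusion.

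The absence of a planned contrast follows directly from SAP 9.4 to 9.7 and needs no assumption. The gain from baseline adjustment depends on assumed correlations: intervals 5% to 29% narrower for r between 0.3 and 0.7. The effect of deaths depends on assumed mortality and EQ-5D values and ranges from 0, with equal mortality, to about 0.07 with a 10-point mortality difference. That the later summaries describe participants alive with data is how the plan will work in practice, not something it declares.

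**What to change.** 1. For EQ-5D, number of medications and number of STOPP medications, add the between-arm difference with 95% CI at 6 and 12 months, and at discharge for the two drug counts. Estimate it from a model with arm, visit, arm-by-visit, baseline value and age stratum.
2. For care level, add a proportional-odds comparison at 6 and 12 months, adjusted for baseline level and age stratum.
3. State that estimates among participants alive with data are conditional on survival, and report deaths by arm beside them. Say how the repeated-measures model respects this: a likelihood-based mixed model implicitly carries values past death, whereas independence estimating equations with robust standard errors do not.
4. Add a sensitivity analysis that includes deaths: for example, death as the worst care category, and EQ-5D scored 0 after death if the index used is anchored at 0 for death. Drug counts have no natural value after death, so item 3 is enough for them.
5. Label these analyses supportive and unadjusted for multiplicity. The revision history shows that analysis had already been conducted by SAP version 1.2, so anything added after that must be labelled post hoc.

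The cost is SAP wording and standard models on data already collected. The downside is small: more analysis work and more unadjusted contrasts to read with care.

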#### 9.5 Level of long-term care required

The level of long-term care required at admission, 6 and 12 months after study enrollment, and their 95% confidence intervals will be calculated for each group.

#### 9.6 Number of regularly prescribed medications and drug name

Descriptive statistics of the number of medications taken at admission, discharge, and 6 and 12 months after study enrollment and the proportion of drug names will be calculated for each group.

#### 9.7 Number of potentially inappropriate medications and drug name

The number of potentially inappropriate prescriptions is defined as the number of medications that meet STOPP criteria, and the names of medications that meet STOPP criteria are defined as potentially inappropriate drug names. Descriptive statistics of the number of potentially inappropriate prescriptions and the proportion of potentially inappropriate drug names will be calculated for each group at admission, discharge, and 6 and 12 months after study enrollment.

#### 9.8 Human and time costs of interventions

Descriptive statistics of the human and time costs of the intervention at each time point will be calculated.

### 10. Safety

#### 10.1 Adverse events

The number of participants in each group who experienced adverse events other than those associated with the primary endpoint and the proportion of such events will be calculated.

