#### 10.3 Adverse events according to event type and severity

The number of participants in each group who experienced adverse events other than those associated with the primary endpoint and the proportion of such events by event and severity will be calculated.

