#### 10.4 List of adverse events

The list of adverse events other than those associated with the primary endpoint will be created.

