#### 10.5 Adverse events associated with the primary endpoint

The number of participants in each group who experienced an event associated with the primary endpoint and the proportion of such events will be calculated.

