#### 10.6 Adverse events associated with the primary endpoint according to event type

The number and proportion of participants in each group with each event associated with the primary endpoint will be calculated.

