#### 10.7 Adverse events associated with the primary endpoint according to event type and severity

The number and proportion of participants in each group who experienced an event associated with the primary endpoint will be calculated according to type of events and event severity.

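### SAP section 10 splits adverse events by association with the primary endpoint and never pools them, so no planned table gives participants by arm with any event, or any event of a given type or grade

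*Combined protocol and SAP*

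**What the plan says.** SAP section 10 plans eight safety outputs in two parallel sets of four.

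- **Events not associated with the primary endpoint.** SAP 10.1 gives "The number of participants in each group who experienced adverse events other than those associated with the primary endpoint". SAP 10.2 repeats this by event type. SAP 10.3 does so by type and grade ("the proportion of such events by event and severity will be calculated"). SAP 10.4 is a listing: "The list of adverse events other than those associated with the primary endpoint will be created".
- **Events associated with the primary endpoint.** SAP 10.5 gives "The number of participants in each group who experienced an event associated with the primary endpoint". SAP 10.6 is by type: "The number and proportion of participants in each group with each event associated with the primary endpoint will be calculated". SAP 10.7 is by type and grade ("will be calculated according to type of events and event severity"). SAP 10.8 is the listing.

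The primary endpoint is the first of rehospitalization, unscheduled visit or death from any cause (Protocol section 7(1)). The only description of an unscheduled visit in either document is in SAP 9.3: any hospital visit without an appointment counts, "regardless of the reason for the visit". Neither document says what makes an adverse event associated with the primary endpoint.

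**The concern.** For an intervention that proposes stopping, reducing or adding drugs, a basic safety comparison is how many participants in each arm had any adverse event, an event of a given type, or an event of a given grade. None of the eight outputs gives that. Each table describes one part of the events, and the parts overlap in participants.

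The dividing line is also a poor one for comparing arms. If an event becomes endpoint-associated because the participant went to hospital without an appointment, then after discharge the same symptom goes in 10.2 when the person stays at home and in 10.6 when they walk in. Care-seeking happens after randomisation, and the trial is open-label (Protocol section 6(1)), so it may be affected by knowledge of the arm. Either half could then show a between-arm difference, or hide one, for reasons unrelated to how often the event occurs.

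**Working it through.** The plan states no figure on this point, so there is none to reproduce. The check has three steps.

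**1. Is any output pooled?** Four outputs (10.1 to 10.4) exclude endpoint-associated events and four (10.5 to 10.8) are confined to them. None combines the two. In addition, 10.3 and 10.7 break severity down within type, so even inside one set there is no row for participants with a severe event of any type.

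**2. Can the total be recovered by adding 10.1 and 10.5?** Let A be the participants in an arm counted in 10.1, B those counted in 10.5, and n the arm size. The number with any adverse event lies between max(A, B), when the smaller group is contained in the larger, and min(n, A + B), when nobody is in both.

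Inputs:
- n = 250 per arm (Protocol section 15; SAP 2.2).
- B = 0.30 × 250 = 75 (intervention) and 0.40 × 250 = 100 (control). This borrows the planned 12-month rates for the composite endpoint and treats every endpoint event as an adverse event. It is an assumption for illustration; the documents give no adverse event rate.
- A is not in the documents. It is assumed equal in the two arms and varied from 25 to 100.

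| A per arm | Intervention: bounds on any event | Control: bounds on any event |
|---|---|---|
| 25 | 75 to 100 of 250 = 30% to 40% | 100 to 125 of 250 = 40% to 50% |
| 50 | 75 to 125 of 250 = 30% to 50% | 100 to 150 of 250 = 40% to 60% |
| 100 | 100 to 175 of 250 = 40% to 70% | 100 to 200 of 250 = 40% to 80% |

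At A = 50 each arm's rate is uncertain by 20 percentage points. The difference, intervention minus control, could be anywhere from 30 − 60 = −30 to 50 − 40 = +10 points, so not even its sign is fixed. The same argument applies to each event type (10.2 with 10.6) and each grade within type (10.3 with 10.7).

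**3. What can the split do to a comparison?** Let p be the proportion of an arm with a given event after discharge, and s the share of those who make an unscheduled visit for it. On the natural reading, 10.6 shows p × s and 10.2 shows p × (1 − s). Assume p = 30% in both arms, with s = 50% in one and 70% in the other:

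- 10.6: 0.30 × 0.50 = 15% v 0.30 × 0.70 = 21%.
- 10.2: 0.30 × 0.50 = 15% v 0.30 × 0.30 = 9%.
- Total: 15 + 15 = 30% v 9 + 21 = 30%.

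The two tables show opposite differences when the true difference is zero. Conversely, if p differs between arms, 10.2 shows no difference whenever p × (1 − s) happens to be equal. This example puts each participant in one table only, so its totals do add; it illustrates the effect of the sorting rule, whereas step 2 illustrates the overlap.

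**The case against.** **Nothing is suppressed.** A reader might infer that events tied to a visit, admission or death drop out of safety reporting. They do not: 10.5 to 10.7 report them by arm, type and severity, and 10.8 lists them. The SAP does not call either set the main one. This stands, and the point is confined to the missing total.

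**The first set need not be mild.** A reader might also infer that 10.1 to 10.3 will hold few severe events by construction. The documents do not support that. Participants are inpatients at allocation with a predicted stay of at least a week (Protocol section 4), and proposals are made within two days of assignment (Protocol section 6(4)). A severe non-fatal event during the index stay is neither a rehospitalization nor an unscheduled visit, so it can fall in the first set. So can an event that prolongs the index stay, which is serious under Protocol section 10(2). Care-seeking therefore bears on the split only after discharge.

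**The sorting rule is inferred.** The term is undefined, and 10.6 could mean tabulation by endpoint component. This stands: step 3 depends on a reading. Step 2 does not.

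**The figures are assumed.** Nothing in the documents shows that care-seeking differs by arm, and the planned 30% and 40% are composite endpoint rates. It would be wrong to read them as the share of participants whose adverse events are moved to the second set, since visits count whatever their reason and need not be adverse events.

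**Other analyses cover the gravest outcomes.** Death and rehospitalization have whole-arm time-to-event analyses (SAP 8.2, 8.4), and falls are reported by group (SAP 9.2). A pooled count could also be derived from the two listings. All true, and it limits the harm, but no such derivation is planned, and other event types and grades have no whole-arm summary.

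**The stated safety endpoint is narrower.** It is adverse events associated with the intervention (Protocol section 7(3)). A pooled table of all events would not by itself report that. This is correct, and is a separate matter.

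**Conclusion.** The point holds as a gap in the safety tables. No planned table gives, by arm, the participants with any adverse event, with an event of a given type, or with an event of a given grade, and the two sets cannot be added because participants can be in both. That conclusion follows from the text of SAP 10.1 to 10.8 and needs only that overlap is possible. Its size is illustrative: 20 percentage points of uncertainty per arm at A = 50, and 10 to 40 points over the range tried.

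The concern about care-seeking rests on three assumptions: the natural reading of an undefined term, an event after discharge, and a difference in care-seeking between arms. It shows what the split could do and does not predict what it will do.

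This should be corrected, because it changes what can be concluded about safety. It does not touch the primary analysis.

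**What to change.** Add to SAP section 10 pooled tables of all adverse events by arm, whether or not associated with the primary endpoint: participants with at least one event overall, by type, and by maximum CTCAE grade, each participant counted once per row. Keep 10.1 to 10.8 as the breakdown of these tables. State the rule that assigns an event to each set, including how events during the index stay are handled.

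SAP version 1.2 records that it was revised after the analysis had been conducted, so the addition should be dated and labelled supplementary.

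The cost is a few more tables. The case report form already collects event details, dates and severity (Protocol section 8(3), secondary endpoints, item 2), so no new data are needed and no efficacy analysis changes.
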